#### Cerebral imaging index

The comprehensive application of multimodal cerebral imaging technology includes the use of rs-fMRI, MRS and DTI based on the BOLD effect. Based on the changes in the functional areas of the cerebral cortex, characteristics of functional connectivity in the whole cerebral cortex, functional connectivity between the cerebral cortex and subcortical nuclei and changes to the white matter and metabolic substances in the cerebral cortex, the objective is to analyse the functional and structural changes of cerebral central sensitization and its neuroimaging mechanism in participants with PDPN.

Based on the above results, participants with PDPN and non-PDPN will undergo multimodal cerebral imaging. The data for both groups will be compared and analysed for changes in cerebral functional areas, characteristics of whole cerebral functional connectivity, abnormal white matter and metabolic changes in the cerebral cortex. The aim of the analysis is to understand the mechanism of electroacupuncture in improving cerebral central sensitization in participants with PDPN.

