**Method and design:**

This will be a randomized controlled trial. A total of 150 participants will be recruited and assigned to one of three groups: the healthy group, the DM without PDPN group and the DM with PDPN group. Participants in the DM without PDPN and the DM with PDPN groups will each be further divided between an electroacupuncture group and a sham electroacupuncture group. Participants will receive six treatment sessions per week for 4 weeks. Multimodal cerebral imaging includes resting-state functional magnetic resonance imaging (rs-fMRI), diffusion tensor imaging (DTI) and magnetic resonance spectroscopy (MRS); this neurophysiological testing will be the primary outcome measure. Subjective pain scales and blood analysis will be a secondary outcome measure and will be used to assess the clinical efficacy of the intervention. Multimodal cerebral imaging will be used to detect cerebral activity changes in each treatment group. The clinical data and fMRI data will be analysed for all the groups. Multiple correlation regression analyses will be used to assess the association between changes in cerebral functional activity and the improvement of clinical outcomes after acupuncture treatment.

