“Adjust Zang Dredge Meridian” electroacupuncture is a therapy established by our research group under the guidance of Chinese acupuncture and the theory of meridian Zang Fu; it incorporates our understanding of the aetiology and pathogenesis of diabetes and its complications. In the pathogenesis of PDPN, seven acupoints have been identified, including Feishu (BL13), Pishu (BL20), Shenshu (BL23), Hegu (LI4), Zusanli (ST36), Sanyinjiao (SP6) and Taichong (LR3). In contrast to the classic acupuncture method of manual twirling, electroacupuncture is safer and more effective in providing pain relief. The combination of classic and electroacupuncture can achieve the effects of regulating zang-fu organs, nourishing meridians and regulating qi and tong jing zhi tong. Based on earlier studies, our research group has demonstrated in both clinical and animal experiments that “Adjust Zang Dredge Meridian” electroacupuncture can effectively improve pain thresholds and nerve conduction velocities in DPN [18, 19]. Therefore, in applying our previous research to the pathological changes of PDPN, we intend to use fMRI technology to explore the potential effects of acupuncture’s central mechanism in the treatment of PDPN. In this proposed study, the first objective will be to use fMRI technology to reveal the mechanisms of central sensitization in the brain of PDPN patients. The second objective will be to investigate the correlation between peripheral neuropathy, subjective pain and changes in brain function in patients with PDPN. The third objective will be to analyse the neuromodulatory effect of “Adjust Zang Dredge Meridian” electroacupuncture on the central sensitization of the brain in PDPN patients through a controlled study of electroacupuncture and sham electroacupuncture and thus to reveal “Adjust Zang Dredge Meridian” electroacupuncture’s mechanism of action in improving the central sensitization of the brain in PDPN patients.

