### rs-fMRI data acquisition

The rs-fMRI scan will be collected with a 3.0 Tesla superconductor (Skyra, Siemens, Erlangen, Germany) in Guang’anmen Hospital. Participants will undergo rs-fMRI scans at baseline and after the 4th week of treatment. Before the scan, participants will be asked to wear earplugs and remove all metal objects from their bodies. Relevant regulations and procedures of the MRI room will be strictly observed. Using foam pads to reduce head movement, participants will be required to remain supine and awake during the entire scan.

Whole cerebral function imaging adopts a T2-weighted echo planar imaging (EPI) sequence for axial scanning, taking the mid-sagittal parallel connection (AC-PC) as the positioning line. Scanning parameters are as follows: number of layers 47, repetition time (TR) = 3000 ms, echo time = 30 ms, layer thickness = 3.0 mm, field of view (FOV) =220 mm × 220 mm, flip angle = 85°, size of voxel = 3.0 mm × 3.0 mm, in-plane resolution = 64 × 64, phase resolution = 100%, and data collection time = 12:30s.

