### Sample size calculation

This proposed study is an RCT whose primary aim is to evaluate the cerebral imaging mechanism of acupuncture to improve cerebral central sensitization and the clinical effect of acupuncture in patients with PDPN. Acupuncture is a complex intervention that differs from other treatments. Its therapeutic effect is changed if the acupoints are altered. No two-arm, randomized, sham-controlled trial has been conducted on this topic. For this reason, we are using our previous clinical experience to calculate the efficacy of electroacupuncture as an intervention [30, 31]. The proposed sample size of this trial was calculated mainly based on the Short-Form McGill Pain Questionnaire and the assumption that after treatment, the average change reported using this questionnaire would be greater for the experimental group than for the control group. The mean difference was 0.81, with a standard deviation of 0.07. Sample size was calculated using a noninferiority comparison. We set the alpha risk (*α*, type 1 error risk) at 0.025, the beta risk (*β*, type 2 error risk) at 0.2 and the critical value (*Δ*) at − 0.1. Calculating by using SAS [32], the sample size result was 24. Thus, according to this sample size calculation, each group should recruit 24 participants. Allowing for a 20% attrition rate in this study, we plan to recruit 150 participants, with 30 in each of the study groups. Healthy participants will not receive any treatment. Each participant will receive 2 rs-fMRI scans to observe different cerebral activities before and after acupuncture treatment.

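### The imaging comparison meant to explain how electroacupuncture improves central sensitization is PDPN versus non-PDPN, which mixes electroacupuncture and sham and cannot isolate the treatment effect

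*Protocol article*

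**What the plan says.** All references are to the protocol article.

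- *Background*, first objective: "the first objective will be to use fMRI technology to reveal the mechanisms of central sensitization in the brain of PDPN patients". The third objective is to study the effect of electroacupuncture on that sensitization by a controlled comparison with sham.
- *Cerebral imaging index*, first paragraph: PDPN changes are characterised across cortical areas, connectivity, white matter and metabolites.
- *Cerebral imaging index*, second paragraph: "Based on the above results, participants with PDPN and non-PDPN will undergo multimodal cerebral imaging". Then: "The data for both groups will be compared and analysed for changes in cerebral functional areas", and further "characteristics of whole cerebral functional connectivity, abnormal white matter and metabolic changes in the cerebral cortex". The stated purpose is: "The aim of the analysis is to understand the mechanism of electroacupuncture in improving cerebral central sensitization in participants with PDPN".
- *rs-fMRI data acquisition*: "Participants will undergo rs-fMRI scans at baseline and after the 4th week of treatment". *Sample size calculation*: "Each participant will receive 2 rs-fMRI scans to observe different cerebral activities before and after acupuncture treatment".
- *Abstract*: "Multimodal cerebral imaging will be used to detect cerebral activity changes in each treatment group".
- *Random allocation*: PDPN 60 and diabetes without PDPN 60, each split 30 electroacupuncture and 30 sham; healthy 30.
- *Neuroimaging data analysis* describes processing, whole-brain and voxel-based methods, and correlations with clinical indices. It names no electroacupuncture-versus-sham test. The analysis of variance of change between groups stands under *Clinical data analysis*.

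**The concern.** The purpose and the comparison do not match. A statement about what electroacupuncture improves needs the randomised contrast. The section instead names a contrast between two clinical populations, each of which contains both arms. The abstract makes imaging the primary outcome, so this concerns the trial's central question: a narrowing PDPN-versus-non-PDPN gap, or a before-after change within an arm, could be reported as the mechanism of electroacupuncture when sham participants changed just as much.

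A second, conditional risk adds to this. The article gives no definition of central sensitization from outside its own PDPN sample. If the regions judged for improvement were those most abnormal at baseline in these same participants, part of their abnormality would be chance and would fade at week 4 by itself.

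**Working it through.** The plan gives no figure for this imaging comparison, so there is none to reproduce. The group sizes come from *Random allocation*; reliability and the share of truly abnormal regions are assumptions.

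**1. What the named comparison estimates.** For any imaging measure, let c_P and c_D be the mean baseline-to-week-4 change under sham in PDPN and in diabetes without PDPN. Let δ_P and δ_D be the extra change from electroacupuncture.

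- PDPN mean change: (30·(c_P + δ_P) + 30·c_P)/60 = c_P + δ_P/2
- Diabetes-without-PDPN mean change: c_D + δ_D/2
- Difference: (c_P − c_D) + (δ_P − δ_D)/2

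If electroacupuncture acts equally in both populations, its effect cancels. If it acts only in PDPN, half of it appears, mixed with c_P − c_D, which randomisation does not control. If non-PDPN also takes in the 30 healthy participants, whom *Sample size calculation* describes as untreated, the non-PDPN share becomes 30/90 = 1/3 of δ_D, and the same difficulty remains.

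Electroacupuncture minus sham within PDPN gives (c_P + δ_P) − c_P = δ_P.

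**2. Precision.** With s the SD of change:

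| Comparison | Standard error | Effect captured (δ_D = 0, no drift) | Effect / SE |
|---|---|---|---|
| Electroacupuncture vs sham, 30 vs 30 | s·√(2/30) = 0.258s | δ_P | 3.87 δ_P/s |
| PDPN vs diabetes, 60 vs 60 | s·√(2/60) = 0.183s | δ_P/2 | 2.74 δ_P/s |
| Pooled PDPN before-after, 60 | s·√(1/60) = 0.129s | δ_P/2 | 3.87 δ_P/s |

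The randomised contrast has twice the standard error of the pooled before-after change, but it captures twice the effect.

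**3. Conditional part: regions carried forward from baseline.** For a region with true standardised difference d, selected because its observed baseline gap g0 was large, and with test-retest correlation ρ, the expected week-4 gap with no treatment effect is d + ρ·(g0 − d). For d = 0 this is ρ·g0, a shrinkage of 1 − ρ.

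Simulation with no treatment effect, PDPN 60 (30 + 30) versus diabetes 60, selection at P < 0.05 (the only P threshold in *Neuroimaging data analysis*, given there for correlations), and no region truly abnormal:

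| ρ (assumed) | Baseline gap (SD) | Week-4 gap (SD) | False improvement, PDPN vs diabetes | False improvement, within electroacupuncture arm |
|---|---|---|---|---|
| 0.3 | 0.43 | 0.13 | 24% | 9.6% |
| 0.5 | 0.43 | 0.21 | 19% | 7.6% |
| 0.8 | 0.42 | 0.34 | 9% | 5.0% |

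The nominal rate in that direction is 2.5%. If 20% of regions are truly abnormal (d = 0.5, assumed), the rates fall to about 4.5% to 13% for PDPN versus comparator and 3% to 5.5% within the arm, over a healthy or diabetes comparator and selection at P < 0.05 or P < 0.001.

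**4. The randomised contrast in the same selected regions.** Both arms drift alike: 0.149 and 0.149 SD at ρ = 0.3, and 0.108 and 0.103 SD at ρ = 0.5 (diabetes comparator, no true abnormality). Two-sided type I error for electroacupuncture versus sham was 4.6% to 5.4% in the P < 0.05 selection runs. This needs regions to be chosen on the pooled PDPN group, not on one arm.

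**The case against.** The strongest reply is that the randomised contrast is in the design. The third objective relies on it, 30 and 30 are randomised within PDPN, and the second paragraph of *Neurophysiological index* speaks of PDPN participants after electroacupuncture and sham. The authors very probably intend it, and a separate analysis plan may say so. This stands as a reason to expect an easy correction. It does not remove the disagreement, because the imaging section does more than stay silent: it names a different comparison and ties it to the treatment aim.

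A reader might go further and infer that the trial selects regions by their baseline PDPN difference and retests them in the same people, so that drift toward normal is built in. The document does not support that. No section states such a selection. The opening phrase of "Based on the above results, participants with PDPN and non-PDPN will undergo multimodal cerebral imaging" also opens the second paragraph of *Neurophysiological index*, where the measures are fixed and nothing can be selected; it reads as a transition from characterisation to treatment. The second imaging step again has whole-brain scope, and the named methods use no mask derived from baseline. A whole-brain analysis of change has no such selection.

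The absence of a region list is also no defect here, since an article commonly leaves that to the analysis plan.

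**Conclusion.** The point holds for the comparison. As written, PDPN versus non-PDPN cannot isolate the effect of electroacupuncture: it carries at most half of the effect in PDPN, loses it entirely if the effect is equal in both populations, and adds a non-randomised difference in drift. It also conflicts with the third objective. This conclusion rests only on the stated allocation and on reading "The data for both groups will be compared and analysed for changes in cerebral functional areas" as referring to the PDPN and non-PDPN participants of the sentence before it.

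Regression to the mean is a conditional addition. It arises only if baseline-abnormal regions are carried forward, and its size depends on test-retest reliability and on the share of truly abnormal regions, neither of which the article gives. Under the assumptions shown, false improvement in PDPN versus comparator ranges from about 4.5% to 24% against a nominal 2.5%, leaving aside P < 0.001 selection with no truly abnormal region, where the rates are higher but rest on few selected regions. Electroacupuncture versus sham stays near its nominal 5%.

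**What to change.** In *Cerebral imaging index* and *Neuroimaging data analysis*, state that the imaging test of improvement is the electroacupuncture-minus-sham difference in baseline-to-week-4 change within PDPN participants, over the whole brain or in regions chosen without regard to arm. Keep PDPN versus non-PDPN for the first objective, the characterisation of central sensitization. Add that within-arm change, and PDPN-versus-non-PDPN change in regions selected at baseline, is descriptive and is not reported as improvement.

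The cost is small. The change is one of wording and needs no new scans. The contrast is 30 versus 30, with a wider interval than a pooled before-after change. A fixed atlas list or split-half selection would also remove the conditional risk, but it may miss unexpected regions, and that choice can be left to the analysis plan.

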#### Neurophysiological index

The SCV of the bilateral superficial peroneal nerve will be measured by EMG. CPT will be performed at 2000 Hz, 250 Hz and 5 Hz, and for each group, the CPT values on the dorsal side of the first bilateral toe will be measured. The Short-Form McGill Pain Scale will be used to evaluate the subjective pain experienced by the subjects in each group. Multiple regression analysis will be performed to analyse the correlation between the SCV, CPT, McGill Pain Scale values and the multimodal cerebral imaging results to reveal and verify the relationship between the degree of peripheral neuropathy, subjective pain and the changes in cerebral function in participants with PDPN.

Based on the above results, the SCV of the bilateral superficial peroneal nerve, the CPT value of the dorsal side of the first toe and the Short-Form McGill Pain Scale will be recorded and evaluated in participants with PDPN after each electroacupuncture and sham electroacupuncture treatment. We will continue to use the method of multiple regression analysis to analyse the correlation between the SCV, CPT, McGill Pain Scale values and the results of the multimodal cerebral imaging to study the relationship between the clinical therapeutic effect of electroacupuncture and the improvement of cerebral central sensitization and reveal the mechanism of electroacupuncture in the treatment of PDPN.

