## Background

Diabetes mellitus (DM) and its complications are serious diseases that harm human health. In 2016, there were approximately 415 million DM patients in the world, or about 8.8% of the global population [1]. In 2019, the 9th IDF Diabetes Atlas, released by the International Diabetes Federation (IDF), shows that there were 116.4 million patients with DM in China, which now ranks as first in the world in the number of DM patients, and this number is expected to reach 142.7 million by 2045 [2]. Diabetic peripheral neuropathy (DPN) is one of the most common complications of DM. In China, approximately 46.6% of DM patients have DPN [3]. Among DPN patients, painful diabetic peripheral neuropathy (PDPN) is a disease that currently lacks effective treatment [3] and has a serious negative impact on a patient’s quality of life [4, 5]. Approximately 11.4% and 40.5% of patients experience severe and moderate pain, respectively, and of these, 3.7% have lower limb ulcers or even required amputations [6]. More than 2/3 of PDPN patients experience varying degrees of problems with depression and anxiety [7, 8], which pose a burden on their families and on society.

PDPN is characterized by distal symmetric polyneuropathy, and the main clinical manifestations are numbness, tingling and abnormal sensations at the end of limbs, which usually start in the lower limbs and are aggravated at night. The pathogenesis of PDPN is very complicated and includes metabolic disorders, vascular injury, nerve injury, oxidative stress and inflammatory responses. In recent years, researchers have generally assumed that peripheral sensitization and central sensitization play an important role in the production and maintenance of PDPN [9–11]. Studies have confirmed [12] that simple peripheral sensitization is not a key factor leading to the occurrence of PDPN. Hyperalgesia and hypersensitivity can still occur after electrical stimulation of the damaged area following anaesthesia. Therefore, central sensitization should be considered a common and core pathological change in PDPN.

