### Participant elimination criteria

Participants that violate the inclusion and/or exclusion criteria.Participants in erroneous treatment groups.In the exit test, participants documenting the use of banned drugs or treatments and participants with incomplete data collection.

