## Outcomes

### Primary outcomes

The primary goal of this study is to observe the degree of peripheral neuropathy and measure the subjective pain perceptions in participants with PDPN before and after acupuncture treatment and assess their correlation with the characteristics of the central sensitization state of the brain. We will measure the sensory nerve conduction velocity (SCV) and the current perception threshold (CPT) and will use the McGill Pain Scale while also combining multimodal brain imaging data for our correlation analysis.

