## Statistical analysis

### Neuroimaging data analysis

Cerebral imaging testing will be entrusted to a third party, professionals of the independent neuroimaging research laboratory at Martinos Center for Biomedical Imaging, Massachusetts General Hospital, Harvard Medical School, USA, for statistical analysis. (1) fMRI data preprocessing: We will use SPM12 for slice timing correction (SPM12, http://www.fil.ion.ucl.ac.uk/spm/), rigid body correction for head motion with the FSL (https://fsl.fmrib.ox.ac.uk/fsl/fslwiki/) [33, 34], subjects with head movement < 1 mm and a rotational shift of < 2° will be entered into the subsequent analysis, bandpass temporal filtering (0.01–0.08 Hz), whole brain signal regression and ventricular and white matter signal regression. We will use the FreeSurfer version 6.0.0 software package to process the structural data and surface mesh representations of the cortex from each participant’s images [35]. Images will be reconstructed and registered to a common spherical coordinate system; functional images will be coregistered to anatomical images and normalized to the MNI152 standard template. (2) Morphological analysis of the grey matter structure of the brain: surface-based morphometry (SBM), voxel-based morphometry (VBM) and morphological analysis of subcortical grey matter structures in the grey matter of the brain will be based on anatomical data. The CIVET-pipeline toolkit and SurfStat software in the MATLAB environment will be used for the processing and statistical analysis of the image data. (3) Analysis of white matter parameters of the brain: Based on DTI scanning, the voxel-based analysis method will be used to process and analyse the test data using the MATLAB toolkit PANDA software. Image processing will include converting images from DICOM format to NIfTI format, eliminating extracerebral tissue and clip aligned images, eddy current correction and realignment, image normalization, calculating tensor and colour maps and fibre tracking and visualization. Finally, FSL software will be used to present the data, and the corresponding white matter fibre bundles will be identified according to the core white matter map of Johns Hopkins University. (4) Brain metabolite analysis: Based on the MRS scanning, images will be converted from DICOM format to RDA format, RDA data will be imported into the LC Model software, GAMMA software will be used in the same sequence and with the same parameters, the absolute concentration of each substance in the imported data will be calculated, and the substance concentration with SD < 15% will be imported into the SPSS 26.0 software package and analysed according to statistical principles. (5) Correlation analysis of SCV, CPT, McGill and multimodal brain imaging research data: Pearson linear correlation analysis in the SPSS 26.0 package will be used to correlate clinical effect indicators such as SCV, CPT and McGill values with the change values from multimodal brain images. The statistical threshold will be set as *P* < 0.05, a Pearson correlation coefficient of *r* > 0 will indicate a positive correlation, and *r* < 0 will indicate a negative correlation. According to the results of the correlation analysis, multiple regression analysis or principal component analysis will be carried out to deeply explore the brain function change characteristics and pathogenesis of brain central sensitization in PDPN.

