
### Clinical data analysis

According to the study data, the effect indices of the two groups will be calculated and compared to analyse the influence on the prognosis of PDPN. Indices of scales will be analysed by repeating measurement analysis of variance. The main analytical indicators will be the curative effect index and recurrence rate. A *t* test will be used for measurement data with a normal distribution. The Wilcoxon rank sum test will be used for nonnormal distribution; the Pearson chi-square test will be used for counting data. If it is a sequential concatenation table, the CMHX^2^ test will be used.

The measurement data of different treatment groups will be statistically described by the mean ± standard deviation (‾*χ* ± s). Intragroup differences will be assessed using a t-test at baseline; analysis of variance (ANOVA) will be used to compare measurement data at different stages; and SNK will be used for pairwise comparisons. Changes between groups before and after treatment will be analysed by ANOVA. If the data do not fit the above statistical analysis conditions (such as nonnormal), a nonparametric test will be used.

Counting data from different treatment groups are statistically described by frequency (constituent ratio). Changes between groups before and after treatment will be tested using the X2 test (CMHX2 test) or nonparametric test. The analysis of data results from participants not complying with the study protocol will be treated according to statistical analysis with randomization and multiple interpolation.

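### Superficial peroneal SCV enters a Pearson correlation as a plain number, so nerves with no recordable response, the most severe ones, fall out of the primary nerve-brain analysis

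*Protocol article*

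**What the plan says.** All places are in the Protocol article.

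- **Primary outcomes.** The stated goal is to relate the degree of peripheral neuropathy and subjective pain to brain findings: "We will measure the sensory nerve conduction velocity (SCV) and the current perception threshold (CPT) and will use the McGill Pain Scale".
- **Neurophysiological index.** "The SCV of the bilateral superficial peroneal nerve will be measured by EMG". The other objective neuropathy measure is a threshold test at the great toe: "CPT will be performed at 2000 Hz, 250 Hz and 5 Hz".
- **Neuroimaging data analysis, item 5.** "Pearson linear correlation analysis in the SPSS 26.0 package will be used to correlate clinical effect indicators such as SCV, CPT and McGill values", at P < 0.05, with multiple regression or principal components to follow.
- **Background.** PDPN is described as distal and symmetric, with symptoms "which usually start in the lower limbs and are aggravated at night". Inclusion requires at least 5 years of diabetes.
- **Participant elimination criteria.** Elimination covers "participants documenting the use of banned drugs or treatments and participants with incomplete data collection".
- **Clinical data analysis.** Data from participants who do not comply with the protocol are handled by "statistical analysis with randomization and multiple interpolation", which I read as multiple imputation. A rank test is allowed for non-normal data.

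No section mentions an absent or unrecordable response.

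**The concern.** Velocity can be computed only when a response is recorded. An absent response is not a slow nerve. It is the worst grade, and it has no number. By the article's own account of the disease, damage is expected first in the legs, where this nerve lies.

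A Pearson coefficient, a regression and a principal component analysis all need a numeric SCV. A participant without one drops out of the SCV analysis whether or not the elimination rule is invoked. If that rule is invoked, the participant's CPT, McGill and imaging data may go too. What is at stake is the second objective, the link between neuropathy and brain function, which would be tested with the severe end of its own scale cut off.

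**Working it through.** **Inputs from the article.** There are 60 PDPN participants, 30 per arm. The sample size section gives 24 per group after 20% attrition, so 2 × 24 = 48 remain. The article gives no power figure for SCV or for the correlation (its sample size rests on the McGill questionnaire), so there is no stated figure to reproduce.

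**Assumptions.** True correlation ρ = 0.5, bivariate normal. The lowest fraction q of nerve function gives no response. The article gives no q, so a range is shown.

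**Formulas.** Let c be the q-quantile of the standard normal and λ = φ(c)/(1 − q).

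- Variance of SCV among recordable nerves: v = 1 + cλ − λ².
- Remaining correlation: r = ρ√v / √(ρ²v + 1 − ρ²).
- Two-sided power at 0.05, with m = 48(1 − q): Φ(atanh(r)·√(m − 3) − 1.96).

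**Full data.** atanh(0.5) = 0.549 and √45 = 6.708, so power is Φ(3.685 − 1.96) = Φ(1.725) = 96%.

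**Worked line, q = 25%.**

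- c = −0.674 and λ = 0.424, so v = 1 − 0.286 − 0.180 = 0.535 (from unrounded values).
- r = 0.5 × 0.731 / √(0.25 × 0.535 + 0.75) = 0.366/0.940 = 0.389.
- m = 36 and atanh(0.389) = 0.410, so power is Φ(0.410 × 5.745 − 1.96) = Φ(0.40) ≈ 66%.

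| Assumed absent share | v | r | m | Power, Pearson on recordable nerves | Power, Spearman with absent ranked lowest (simulated) |
|---|---|---|---|---|---|
| 0% | 1.000 | 0.50 | 48.0 | 96% | 93-94% |
| 2% | 0.896 | 0.48 | 47.0 | 93-94% | 94% |
| 5% | 0.810 | 0.46 | 45.6 | 90% | 93% |
| 10% | 0.712 | 0.44 | 43.2 | 85% | 94% |
| 25% | 0.535 | 0.39 | 36.0 | 66% | 93% |
| 40% | 0.422 | 0.35 | 28.8 | 46-47% | 91% |

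Where a range is given for Pearson, formula and simulation differ by about a point. The rank method gains nothing at 2% and gains clearly from 10% upward.

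**Weaker true correlation.** With ρ = 0.3 and all 60 participants, power falls from 65% to 54% at 5% absent and to 36% at 20%.

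**What is not biased.** Dropping low SCV values leaves the slope of brain measure on SCV unchanged (0.50 throughout in simulation). The slope of SCV on brain measure and the Pearson r are both affected, and the article tests r.

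**Arm comparison.** The clinical analysis section compares changes before and after treatment, so the relevant quantity is SCV change among nerves recorded at both visits.

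- Same effect in every nerve (0.3 SD, retest correlation assumed 0.7-0.9, 10-40% absent): about 77-96% of the effect remains.
- Other response patterns (effect 0.2-0.4 SD, retest 0.9, 5-50% absent): the ratio to the full effect runs from 1.03 to 1.81 if the worst nerves do not respond, and from 0.93 down to 0.57 if they respond twice as much.

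The direction is therefore not determined.

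**The case against.** **The rules do not name absent responses.** A reader might infer that the plan deletes or imputes the worst nerves by rule. The text does not say so. An attempted recording with no response can fairly be called collected data, and the imputation sentence is worded for participants who do not comply with the protocol. Both objections stand: applying the elimination rule here is a possible reading, and applying imputation is not supported. The loss from the Pearson analysis needs neither rule.

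**Coding belongs in the SAP.** Usually it does, and silence alone would be no finding. Here, however, the article itself fixes a numeric SCV, a Pearson test and an elimination rule. An SAP that followed them would inherit the problem.

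**The treatment effect.** A reader might infer that the effect on SCV is shrunk, or that recovery from no response to a slow one counts as worsening. That would hold for a comparison of post-treatment means. In a change analysis, a nerve with no baseline velocity does not enter, and the simulated ratios fall on both sides of 1.

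**The rate is unknown.** This stands. The site of the nerve and 5 years of diabetes do not establish a rate, and serious diabetic complications are excluded. At 2-5% the loss is small.

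**Mitigations.** Recording is bilateral. With an assumed side-to-side correlation of 0.8, 10% absent per nerve leaves about 6% absent on both sides. CPT and the MNSI also measure neuropathy. These soften the loss for the objective as a whole but do not repair the SCV correlation.

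**Conclusion.** The point holds in limited form. As written, the SCV-imaging correlation excludes the most severe nerves, and the elimination wording leaves room to exclude the participants as well. With a true correlation of 0.5 and 48 participants, power falls from 96% to about 94-90% at 2-5% absent, 85% at 10%, 66% at 25% and 47% at 40%. These figures rest on a linear bivariate normal model, on absence that strictly follows severity, and on shares that the article does not give. For SCV change between arms, the documents support only a distortion of unknown direction. They do not establish that the plan imputes absent responses or that the treatment effect is shrunk. It is worth fixing because the remedy is cheap and loses little even if the problem proves rare.

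**What to change.** - **Participant elimination criteria:** state that an absent response on an attempted recording is a result, not incomplete data, and is no ground for elimination.
- **Neuroimaging data analysis, item 5:** rank an absent response as the worst SCV value and use Spearman in place of Pearson correlation for SCV. State how the two sides are combined when only one responds.
- **Clinical data analysis:** state that absent responses are not imputed, and compare the arms on SCV by a rank-based method with absent ranked lowest. The section already allows a rank test for non-normal data.
- **Supportive only:** response amplitude, set to 0 when absent. Replacing SCV by amplitude would change a measure listed under primary outcomes and is not needed.

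The cost is wording, settled before database lock, with no new visits or participants. If every nerve proves recordable, power is about 94% against 96%.
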